### Side-effects of chemotherapy

Adverse events of the conventional cancer treatment will be documented according to the international standard of the National Cancer Institute (NCI) Common Terminology Criteria for Adverse Events [60].

### Sample size and power considerations

Sample size was calculated for the global quality of life (Items 29 and 30 of EORTC-QLQ-C30) and was based on a two-group comparison using Student’s t-test because no reliable estimate of the correlation between repeated measures was available. Following the recommendation by Cocks *et al*. [36], a difference of 10 points between the randomized groups was considered clinically important (that is, ‘smallest medium difference’). This difference corresponds to a standardized effect of d = 0.4 according to Cohen. To detect d = 0.4 with a power of 1 - β = 80% using a two-sample t-test at a two-sided significance level α = 5%, a total of 200 patients in the randomized arms (100 per arm) will be required. The sample size calculation was performed using nQuery Advisor V7.0. We expect the power of the main statistical analysis to be higher than 80% because repeated measurements will be taken into account and the analysis will be additionally adjusted for relevant covariates such as HRQoL at baseline.

We assume that 40% of the patients have no or no strong preference and thus will be randomized. About 60% of the patients are assumed to have a strong preference for the CAM intervention. Therefore, we need to include 200 patients in the randomized arms (100 per arm) and we expect to include about 300 patients in the observational arms. Assuming up to 15% of patients may not have primary outcome data available, the sample size was adjusted to a total of 236 patients in the randomized arms (118 per arm) and about 354 patients in the observational arms.

### Data analysis

According to Schmoor *et al.* [61], the first analysis step of PRPP trials is the classical analysis of the randomized patients. These are the basic results of the trial and these results have internal validity. The primary objective of the present study is to determine the effectiveness of a complex nursing care intervention on CAM in women with breast and gynecologic cancer undergoing chemotherapy, and to show that the complex intervention results in higher HRQoL, compared to usual nursing care alone. The primary endpoint is the global HRQoL subscale of the EORTC QLQ-C30 questionnaire and is assumed to follow an approximate normal distribution [35].

A linear mixed model will be used to compare HRQoL under chemotherapy between the two randomized groups from treatment start to long-term follow-up (T1 to T4). This model takes into account the hierarchical structure of the data with repeated measurements nested in patients (that is, patients will be included as random effects in the intercept). Fixed effects will include treatment (usual nursing care versus complex nursing care intervention on CAM), the time of measurement (T1 to T4), the interaction of treatment and time, as well as the HRQoL baseline scores at T1, and the stratification variables stage of cancer (non-metastatic versus metastatic) and study centre (university hospital versus community hospital). Because the measurements are not equidistant in time, an unstructured covariance matrix will be estimated. For the main effect of treatment, the null hypothesis of no difference in group averages will be tested at the two-sided significance level of α = 0.05. Differences between short-term and long-term effects will be assessed by the interaction of treatment and time. The primary analysis will be performed for all randomized patients according to the intention-to-treat principle. As sensitivity analysis, the analysis will be repeated in the per protocol set, excluding patients with major protocol violations. Because longitudinal mixed models make use of the missing at random assumption, no imputation will be used to handle missing data in the primary analysis. However, sensitivity analyses will be conducted to assess the impact of missing data (for example, omitted measurements at some time point) by various approaches, including for example the ICA-r method (imputation according to reasons for missingness [62]), the last observation carried forward, and multiple imputation. Model fit will be assessed by visual inspection of residual plots. Descriptive analyses of secondary endpoints will be performed. All estimates will be presented with 95% confidence intervals. External validity will be assessed by comparing the randomized with the non-randomized patients. The comparison of the observational group will thereby facilitate the applicability of the results. The central part of the second analysis step is, thus, to assess whether treatment effects observed in the randomized patients are comparable with those observed in the two observational arms. If there are measurable differences between these two groups with regard to prognostic factors, the effect of these differences will be examined using propensity score methods. Propensity scores will be determined that reflect the patients’ preferences.

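### The primary mixed model uses the T1 quality-of-life score both as a response and as the baseline covariate, so it has no maximum under the stated covariance and understates the effect if simplified

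*Protocol article*

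**What the plan says.** All of the following is in the protocol article. Under Data analysis, the primary model compares quality of life "between the two randomized groups from treatment start to long-term follow-up (T1 to T4"). Its fixed effects are treatment, "the time of measurement (T1 to T4), the interaction of treatment and time, as well as the HRQoL baseline scores at T1", and the two stratification variables. For the correlation within patients, the section says that "patients will be included as random effects in the intercept" and also that "Because the measurements are not equidistant in time, an unstructured covariance matrix will be estimated".

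The confirmatory test is defined thus: "For the main effect of treatment, the null hypothesis of no difference in group averages will be tested", two-sided at 5%. The interaction has its own purpose: "Differences between short-term and long-term effects will be assessed by the interaction of treatment and time". Estimates are to carry 95% confidence intervals.

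Table 1 labels T1 as baseline and start of intervention, and the Schedule section describes it as the start of the intervention. Table 1 schedules the EORTC QLQ-C30 at T1, T2, T3, T4 and weekly in the diary, but not at T0. T1 is therefore the only pre-intervention questionnaire value, and nothing in the article removes T1 from the response.

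**The concern.** A baseline value can enter a longitudinal model as a covariate or as a response. Here it does both. In the T1 rows the model regresses a number on itself, with three possible consequences:

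- Under an unstructured covariance, the fit can make the T1 rows perfect by setting the baseline slope to 1, which breaks the likelihood.
- If a simpler covariance lets the model be fitted, the tested average over four visits includes one at which no effect is expected, so the reported effect is too small as a measure of benefit under the intervention.
- A treatment-by-time test that includes T1 partly asks whether any effect appears after baseline, which is not the short-term versus long-term question the article sets.

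This is the trial's primary analysis, so its specification should be one that can be carried out and that estimates the effect of interest.

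**Working it through.** **Inputs.** From Sample size and power considerations: 10 points, d = 0.4, 100 per arm. From Data analysis: responses T1 to T4, T1 as covariate, random intercept, unstructured covariance. Assumed, because the article gives no correlation: exchangeable correlation ρ of 0.3, 0.5 or 0.7, complete data, and true effects of 0, 10, 10, 10 points at T1 to T4. The zero at T1 rests on T1 being the baseline.

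**The plan's own figures.** The implied SD is 10/0.4 = 25. A two-sample t-test with d = 0.4, 80% power and two-sided 5% needs 99.08, so 100 per arm (power 80.4%). Inflation gives 200/0.85 = 235.3, so 236. Both stated figures reproduce.

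**Step 1: unstructured covariance.** Take one slope β for the T1 score and free treatment-by-time means. Subtracting β·Y1 from every visit multiplies the T1 residual by (1 − β) and leaves the covariance of T2 to T4 given T1 unchanged. The determinant of the residual covariance is therefore (1 − β)² times a constant, and with n = 200 the profile log-likelihood is

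logL(β) = logL(0) − 200·ln(1 − β).

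For one simulated data set (ρ = 0.5), with logL(0) = −3573.7:

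| β | T1 residual variance | logL |
|---|---|---|
| 0 | 533 | −3573.7 |
| 0.5 | 133 | −3435.0 |
| 0.99 | 0.053 | −2652.6 |
| 0.999999 | 5 × 10⁻¹⁰ | −810.6 |
| 1 − 10⁻⁹ | 5 × 10⁻¹⁶ | +571.0 |

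There is no finite maximum, whatever ρ is. Adding stage and centre, or using REML, does not help: in a separate simulated data set the slope went to 0.99999 in 14 iterations while the REML log-likelihood rose from −2785 to −729.

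**Step 2: random intercept only.** With complete data, the treatment effect averaged over visits is the treatment coefficient in a regression of each patient's mean on treatment and Y1. Let M be the mean of T2 to T4. The patient mean is (Y1 + 3M)/4. Adjusted for Y1, the Y1 part contributes nothing to the treatment coefficient or the residual, so estimate and standard error are both exactly 3/4 of those for M. Averages over 4,000 simulated trials per ρ:

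| ρ | T1–T4: estimate (SE) | T2–T4: estimate (SE) | Power, both |
|---|---|---|---|
| 0.3 | 7.53 (1.77) | 10.04 (2.36) | 99% |
| 0.5 | 7.47 (1.72) | 9.96 (2.29) | 99% |
| 0.7 | 7.47 (1.48) | 9.96 (1.97) | 99.9% |

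In standardized terms, 7.5/25 = 0.30 instead of 0.40. Mixed-model fits to one data set agree: 6.70 against 8.93, ratio 0.75. The baseline slope is distorted as the algebra predicts: (1 + 3 × 0.589)/4 = 0.692, and the fit gave 0.692.

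**Step 3: treatment by time.** In the random-intercept fit, the within-patient residual variance is 625(1 − ρ). The effects 0, 10, 10, 10 have mean 7.5 and squared deviations 56.25 + 3 × 6.25 = 75. The noncentrality is 75 × (100/2)/[625(1 − ρ)] = 6/(1 − ρ), which is 8.6, 12 and 20. A test on 3 and 594 degrees of freedom then rejects with probability 68%, 84% and 97%. Simulation (600 trials) gave 69%, 85% and 97%. Restricted to T2 to T4, where the true effects are equal, it rejected in about 5.5%.

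**The case against.** The strongest reply is that the confirmatory test survives wherever the model can be fitted. That is right: estimate and standard error shrink by the same factor, so the p-value does not change. A reader might infer a loss of power; there is none in the random-intercept fit. Even if the unstructured fit were pushed to its change-score limit, the standard error would be 14% to 45% larger than with baseline adjustment, and power for 10 points would still be about 83%, 93% and 99% for ρ of 0.3, 0.5 and 0.7, above the planned 80%.

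Other stronger readings also go too far:

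- **Failure and attenuation together.** They are alternatives: the unbounded likelihood belongs to the unstructured covariance, the 7.5 points to the random intercept alone.
- **Ten points as a success threshold.** The article says "a difference of 10 points between the randomized groups was considered clinically important", but uses this to size the trial. The tested hypothesis is no difference, and the interval around 7.5 is not miscalibrated for a T1 to T4 average. The complaint is that this average is a poor target.
- **T1 effect zero by construction.** At a slope below 1 it is zero only in expectation; the fitted data set gave 0.47.
- **Main effect as a T1 contrast under reference coding.** The article's definition by group averages excludes that.
- **Random intercept plus unstructured matrix.** If both are meant, only the split of variance is unidentified; the marginal covariance that drives inference on treatment is not harmed by the redundancy.
- **A replacement model chosen after seeing the data.** An analysis plan not shown may settle the model, and a failed fit could be found on blinded data.

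One could also read T1 to T4 as merely the span of the study. The text does not allow it, because it names T1 to T4 as the values of the time factor. Nor is this a detail left to an analysis plan: the article states the specification itself.

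**Conclusion.** The point holds as an error in stated text. As written, with the unstructured covariance, the primary model has no valid maximum; this does not depend on the correlation or the effect size. With a random intercept only, the model can be fitted, but the reported average is three quarters of the T2 to T4 effect, so a constant 10 points appears as about 7.5. The factor of 3/4 is exact with complete data and does not depend on ρ. The figure of 7.5 also assumes a constant effect at T2 to T4 and none at T1. The damage is to the effect size and its confidence interval, not to the p-value or power.

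The treatment-by-time test is a supporting analysis, but with T1 included it does not answer the question set for it. The 69% to 97% rejection rates rest on the random-intercept fit, SD 25, 100 per arm, exchangeable correlation of 0.3 to 0.7 and a constant 10-point effect.

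The specification has to be corrected because the primary model cannot be fitted as stated.

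**What to change.** Amend the model description as follows:

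1. Use T2, T3 and T4 as the responses, with T1 quality of life as covariate. Alternatively, keep T1 as a response with a common baseline mean in both arms and drop the T1 covariate.
2. Define the primary test as the treatment difference averaged over T2 to T4.
3. Test treatment by time over T2 to T4 only.
4. State one covariance specification: an unstructured residual matrix, without the redundant random intercept.

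The cost is wording in the protocol and in any analysis plan that repeats it. No new data are needed, and the randomized sample size of 200, inflated to 236, does not change because it comes from a t-test on a single difference.

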### Recruitment and randomization

Informed consent will be obtained from all women before study entry. Breast and gynecological cancer patients registering for a new chemotherapy regime at the National Centre for Tumour Diseases (NCT) Heidelberg and the Community Hospital Karlsruhe will be informed by flyer, their treating oncologist, or nursing staff about the CONGO study. Then, a CAM-trained nurse will approach the potential participant, briefly inform her about the study and ask her if she would like to have further information. Those agreeing will be provided with details of the study verbally and in written form via the study information leaflet. Patients who agree to participate will be asked to sign the consent form. After informed consent, baseline assessments will be conducted. The nurse will assert if the potential participant has a strong preference to receive the CAM nursing intervention and allocate her into the observational part of the study if applicable. All other participants will be allocated into the randomized part.

The CAM-trained nurses will randomize the study participants using *randomizer.at*, which is an online central randomization service. Participants will be stratified by cancer center (NCT Heidelberg/Community Hospital Karlsruhe) and stage of cancer (curative treatment/palliative treatment), and then randomly allocated at a ratio of 1:1 to the intervention or control arm of the randomized part of the trial. Blocked randomization with varying block sizes will assure that the numbers in the arms are balanced, while the nurses are not being given the possibility to deduce the next allocation. Further, allocation concealment will be ensured, as the randomization service does not release the code for the randomization done by the CAM-trained nurse administering the intervention. Thus, it will be assured that the recruiter has no knowledge about the random sequence and hence cannot influence participants due to possible bias.

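### The stage stratum is curative versus palliative treatment at randomization but non-metastatic versus metastatic in the primary model, which still calls it a stratification variable

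*Protocol article*

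**What the plan says.** In Recruitment and randomization, participants are "stratified by cancer center (NCT Heidelberg/Community Hospital Karlsruhe) and stage of cancer (curative treatment/palliative treatment"), then "randomly allocated at a ratio of 1:1 to the intervention or control arm of the randomized part of the trial". Blocks vary in size.

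In Data analysis, the fixed effects of the primary linear mixed model are treatment, time, their interaction, baseline HRQoL, and "the stratification variables stage of cancer (non-metastatic versus metastatic) and study centre (university hospital versus community hospital").

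Both sections use the label stage of cancer, and the second expressly calls its factor a stratification variable. The two-level definitions in brackets are not the same.

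**The concern.** When allocation is blocked within strata, the arms are balanced on the stratification factors by design. An analysis that conditions on those factors gives a standard error that reflects this balance. If the model carries a different variable, the balance is only partly credited, so the model-based standard error tends to be somewhat too large and the test slightly conservative.

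The discrepancy sits in the single primary model, tested at two-sided 0.05. The Sample size and power considerations section also expects power above 80% partly because the analysis adjusts for relevant covariates, and a covariate that only approximates the stratum delivers less of that gain.

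There is a practical route to the problem as well. Table 1 lists cancer characteristics as collected at T0. Someone programming from the Data analysis section could take metastatic status from the clinical record instead of the stratum entered at randomization.

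**Working it through.** **1. The two definitions side by side**

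| Factor | Recruitment and randomization | Data analysis | Same? |
|---|---|---|---|
| Centre | NCT Heidelberg / Community Hospital Karlsruhe | university / community hospital | Yes: Participants and setting names one university and one community hospital |
| Stage | curative / palliative treatment | non-metastatic / metastatic | Not as written: intent versus extent, with no mapping anywhere |

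**2. The plan's own figures**

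The inputs, from Sample size and power considerations, are a difference of 10 points, d = 0.4, 80% power, two-sided 5% and up to 15% missing.

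- Implied SD: 10 / 0.4 = 25 points.
- Normal approximation: n per arm = 2(1.960 + 0.842)² / 0.4² = 98.1, so 99.
- Exact two-sample t-test: 99.08, so 100 per arm, with power 80.4%.
- Missing data: 200 / 0.85 = 235.3, so 236 (118 per arm).

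The stated 200 and 236 reproduce. The calculation is an unadjusted t-test, so neither figure depends on how stage is defined.

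**3. Size of the consequence (illustrative; none of these inputs is in the article)**

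The simulation had 200 patients, 30% palliative, blocks of four within the stage stratum, a single endpoint with within-stratum SD 1, and 4,000 runs per scenario. The treatment effect was 0 for type I error and 0.4 for power. The stratum effect was 0.4 or 0.8 SD (10 or 20 points on an SD of 25). A random 5%, 10% or 20% of patients were classified differently by the second coding. Each model had treatment arm plus one stage factor: either the true stratum or the differing variable.

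| Stratum effect | Discordance | Type I error, true / differing | Power, true / differing | Mean SE (null runs), true / differing | SE ratio |
|---|---|---|---|---|---|
| 0.4 | 5% | 0.0520 / 0.0540 | 0.8062 / 0.8068 | 0.1411 / 0.1417 | 1.004 |
| 0.4 | 10% | 0.0512 / 0.0512 | 0.8075 / 0.8035 | 0.1412 / 0.1423 | 1.008 |
| 0.4 | 20% | 0.0478 / 0.0465 | 0.8050 / 0.7945 | 0.1413 / 0.1431 | 1.013 |
| 0.8 | 5% | 0.0550 / 0.0525 | 0.7995 / 0.7897 | 0.1411 / 0.1433 | 1.016 |
| 0.8 | 10% | 0.0498 / 0.0450 | 0.8108 / 0.7897 | 0.1412 / 0.1450 | 1.027 |
| 0.8 | 20% | 0.0503 / 0.0418 | 0.8005 / 0.7712 | 0.1414 / 0.1480 | 1.047 |

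The power loss runs from nil (-0.06 points) to 2.9 points (0.8005 - 0.7712). Type I error with the differing variable lies between 0.042 and 0.054. The Monte Carlo standard error at 0.05 is √(0.05 × 0.95 / 4000) = 0.0034, so 0.054 is compatible with 0.05, and the low values show mild conservatism. In the worst scenario the mean model-based SE is 0.1480 against an actual SD of the estimate of 0.1439, an overstatement of 0.1480 / 0.1439 - 1 = 2.8%. The rest of the 4.7% is a real loss of precision.

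**4. Bias**

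This follows from the design rather than from the simulation. Both codings describe the patient before allocation, so adjusting for either leaves the randomized comparison unbiased.

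**The case against.** The strongest reply is that this is loose wording for one recorded variable. The same sentence of Data analysis also relabels centre without changing it, both sections say stage of cancer, and the operational definition of a covariate is often settled in an analysis plan, which is not shown. This reading is possible, and it rules out stating as fact that the model uses a different variable. It does not remove the contradiction: the centre labels can be matched from the article itself and the stage labels cannot. An analysis plan written from this text would inherit the conflict.

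Three stronger readings are tempting, and the article does not support them.

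- **That the true stratification factor is left out.** Complete omission would inflate the standard error by 1/√(1 - R²): 1.010, 1.026 and 1.054 for assumed R² of 0.02, 0.05 and 0.10. The plan does include a stage factor, and it presumably overlaps with treatment intent. With an assumed correlation of 0.8 between the codings, the inflation is √((1 - 0.64R²)/(1 - R²)), or 1.004 at R² = 0.02 and 1.020 at R² = 0.10.
- **That the benefit of stratifying is thrown away.** The balance comes from the stratified, blocked allocation and remains whatever covariate is modelled.
- **That the analysis is left open to a free choice between codings.** Data analysis names one coding. What is unclear is whether that coding is the randomization stratum.

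It is also tempting to argue from clinical examples in which intent and extent diverge. The article gives none and no discordance rate, so the point rests only on the two stated definitions.

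**Conclusion.** The point holds as an inconsistency in the specification of the primary model. One label carries two definitions, and the one in the model is called a stratification variable although randomization is described with the other. If the classifications agree for every patient, only the wording is wrong. If they do not, the model does not fully condition on the randomization factor, and the likely result is slight conservatism and a small loss of precision.

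The figure of about 0 to 3 points of power rests on the assumed 30% palliative share, the stratum effects of 0.4 and 0.8 SD, discordance of 5% to 20%, and a single-endpoint model without baseline HRQoL, centre or repeated measures. It indicates an order of magnitude and is not a forecast for this trial. A reader might infer bias, an invalid test or an inadequate sample size; none of these follows.

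**What to change.** In Data analysis, replace the bracketed definition of stage with: curative versus palliative treatment, as recorded in the randomization system. Keep study centre as it is. If metastatic status is wanted, name it in advance as an additional covariate or confine it to a sensitivity analysis. If the sponsor regards the two descriptions as the same variable, say so and use one wording in both sections.

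The cost is one phrase. The stratum is already recorded at randomization, so no new data are needed, and the sample size stays at 200 and 236. The change should be made before any comparative data are examined.

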**Figure 2 Fig2:**
[figure not shown]
**Timeline.** EOI, end of intervention; FU, follow- up; IC, informed consent; ICI, initial counseling interview; SOI, start of intervention.

T0: Baseline assessment 1 to 2 weeks before the start of chemotherapy).T1: Start of intervention (SOI).T2: Mid-line (after the first half of the chemotherapy regimen; maximum of 12 weeks).T3: End of intervention (EOI) (after the end of the chemotherapy; maximum 24 weeks).T4: Follow-up, 6 months after the completion of chemotherapy (after maximum of 48 weeks).

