### Quality of life (patients)

The main outcome measure HRQoL will be measured with the global quality of life scale of the European Organization for Research and Treatment of Cancer Quality of Life Questionnaire (EORTC-QLQ-C30) [35-37]. The QLQ-C30 is a 30-item questionnaire developed to assess the HRQoL and five multi-item functional scales (physical, role, emotional, cognitive, and social function), three multi-item symptom scales (fatigue, pain, and nausea/vomiting), and six single items assessing further physical symptoms (appetite loss, constipation, diarrhea, dyspnea, and insomnia) and financial difficulties. The global quality of life will be calculated from two items (item 29 ‘overall health last week’ and item 30 ‘overall HRQoL last week’) , which are measured in seven interval Likert scales and then combined and transformed into a scale between 0 and 100 points. In the planned trial, the HRQoL will be assessed at all assessment points T1, T2, T3, T4, and weekly in the patient diary.

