## Discussion

The CONGO study is the first prospective partially randomized patient preference trial investigating the impact of a nurse-led intervention involving both clinic and home-based CAM use in breast and gynecologic cancer patients undergoing chemotherapy in two outpatient cancer services. The findings from this study will add to the growing body of evidence of the effectiveness of CAM interventions for individuals with cancer, by testing several aspects relevant for the implementation of patient-centered models of integrative healthcare: (1) patients will receive cancer care including CAMs and individual counseling on CAM by oncology nurses; (2) patients’ preference to receive the CAM intervention will be considered; (3) patients’ empowerment resources will be activated in the initial and following individualized counseling interviews, by receiving standardized CAM instructions and an additional information booklet including evidence-based CAM for home use; (4) The effect of the intervention will be measured on HRQoL and a range of other physical and psychosocial symptoms; (5) Sustainability and long-term effects of this intervention will be assessed by follow-up; (6) A thorough process evaluation will provide explanation on succeeding or impedimental factors impacting concomitantly on the process of the intervention.

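### The treatment-by-time interaction meant to compare short- and long-term effects includes the baseline visit T1, so it mainly detects that an effect exists, not whether it lasts

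*Protocol article*

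**What the plan says.** The Data analysis section of the protocol article fits a linear mixed model to global HRQoL. Its fixed effects include treatment and "the time of measurement (T1 to T4), the interaction of treatment and time, as well as the HRQoL baseline scores at T1". T1 is therefore a level of the time factor, and the T1 score is also a covariate. A null hypothesis and a significance level are given for the main effect of treatment. For the durability question the section says only: "Differences between short-term and long-term effects will be assessed by the interaction of treatment and time". It names no contrast between particular visits.

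The timeline under Schedule defines the first modelled visit as "T1: Start of intervention (SOI"), and Table 1 heads the same column as baseline. T2 falls midway through chemotherapy and T3 at its end. The last visit is "T4: Follow-up, 6 months after the completion of chemotherapy (after maximum of 48 weeks"). The two items behind the endpoint are "item 29 ‘overall health last week’ and item 30 ‘overall HRQoL last week" (section Quality of life, patients), so a T1 answer looks back over the week before the intervention begins. The Discussion lists durability among the aspects the study will test: "Sustainability and long-term effects of this intervention will be assessed by follow-up".

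**The concern.** An interaction over T1 to T4 asks whether the arm difference is the same at all four visits. At T1 it is zero in expectation, because allocation is randomized and the intervention has not yet acted. Equality across the four visits therefore means no effect at any of them. If the intervention works and its benefit is fully kept, the null hypothesis is false and the test tends to reject. Read as a comparison of short- with long-term effect, that rejection would say the two differ when they are the same. The study could then give a wrong answer to a question it sets itself, in the very situation its investigators hope for.

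**Working it through.** **Inputs.** From Sample size and power considerations: a difference of 10 points, d = 0.4, two-sided 5%, 80% power, 100 per arm, and 118 per arm after allowing for 15% without primary outcome data. Implied SD = 10/0.4 = 25. The section says that no reliable estimate of the correlation between repeated measures was available, so the correlation ρ is an assumption here, shown over a range.

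**The plan's own figure.** For d = 0.4 the two-sample t-test needs 99.08 per arm, hence 100, with power 80.4%. 200/0.85 = 235.3, hence 236. Both stated sizes reproduce.

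**The interaction as specified.** Take time as a four-level factor, equal correlation ρ between visits and complete data. The arm difference at one visit has variance 2 × 25²/100 = 12.5. The 3-df interaction has noncentrality

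λ = Σ(δⱼ − mean δ)² / [12.5(1 − ρ)],

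and is referred to a noncentral F with 3 and 196 df (unstructured covariance).

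Sustained 10 points, δ = (0, 10, 10, 10): the mean is 7.5 and the sum of squares is 7.5² + 3 × 2.5² = 75, so λ = 6/(1 − ρ). Sustained 5 points: the sum is 18.75, so λ = 1.5/(1 − ρ).

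| ρ | λ, 10 points | P(significant) | λ, 5 points | P(significant) |
|---|---|---|---|---|
| 0 | 6.0 | 51% | 1.5 | 15% |
| 0.3 | 8.6 | 68% | 2.1 | 20% |
| 0.5 | 12.0 | 83% | 3.0 | 27% |
| 0.7 | 20.0 | 97% | 5.0 | 43% |

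In every row the effects at T2, T3 and T4 are equal, so a valid short- versus long-term test would reject in 5%.

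**Sensitivity.** For the sustained 10-point effect, correlation that decays with visit distance (AR(1) with 0.3, 0.5, 0.7) gives 58%, 70% and 89%. With 118 complete patients per arm and equal correlation 0.3, 0.5, 0.7, the figures are 76%, 89% and 99%.

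**Does the T1 covariate repair it?** No. In complete balanced data a patient-level covariate leaves the within-patient interaction unchanged. Simulating the random-intercept model with T1 as both outcome and covariate (300 runs per correlation, 100 per arm) gave 70%, 84% and 98% at ρ = 0.3, 0.5, 0.7.

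**T1 removed.** The interaction over T2 to T4 only (2 df) rejects in 5% under a sustained effect (simulated 4.0% to 4.7%).

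**Single contrasts.** Effect at T4 minus effect at T3: SE = √[2 × 12.5(1 − ρ)] = 4.18, 3.54, 2.74 at ρ = 0.3, 0.5, 0.7. It rejects in 5% under a sustained effect. Power is 66%, 80%, 95% for a complete fade from 10 to 0, and about 22%, 29%, 44% for a fade from 10 to 5. Effect at T4 minus the T2/T3 average: SE = √[1.5 × 12.5(1 − ρ)] = 3.62, 3.06, 2.37. Effects of 10, 10, 5 at T2, T3, T4 are detected with power of about 28%, 37%, 55%.

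**The case against.** **No decision rule is stated.** The plan attaches a null hypothesis and alpha only to the main effect. For the interaction it names no omnibus test, degrees of freedom or threshold. A T4-against-T3 comparison is itself a contrast of the interaction terms, estimates are promised with 95% confidence intervals, and a condensed article may leave the choice of contrast to the analysis plan. This stands as far as it goes: the wording does not forbid a suitable contrast. But the article does not merely leave a detail open. It names the interaction, defines time to include T1, and names nothing else. An analysis plan that follows it inherits the fault.

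**The fault comes from using T1 as an outcome.** This is true, and for an effect that is constant after baseline, removing T1 is enough. A reader might infer that removing T1 is no cure, because with effects of 5, 10 and 10 points the 2-df test over T2 to T4 still rejects in 21%, 29% and 45% of trials (ρ = 0.3, 0.5, 0.7). The documents do not support calling those rejections false. They never define short-term as T3 alone, and if it includes T2, then 5 at T2 against 10 at T4 is a real difference.

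**Not every working intervention is flagged.** A reader might infer that any effective intervention yields a significant interaction. The 5-point figures of 20% to 43% show otherwise. At that effect, rejection of the interaction is several times too frequent as a test of short against long term, but it is not the usual outcome.

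**Conclusion.** The point holds. As written, the interaction answers whether the arms diverge at all after baseline, not whether the early and late effects differ. At the planning effect of 10 points, sustained in full, it is significant in about 68% to 97% of trials, and in about 51% even with no correlation between visits. At a sustained 5 points the range is about 20% to 43%. The valid rate is 5%.

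These figures rest on SD 25, 100 complete patients per arm, time as a categorical factor, no arm difference at T1, and equal correlations of 0.3 to 0.7 that the protocol does not supply. The direction of the error does not depend on the correlation; its size does.

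The point is confined to the short- versus long-term conclusion. It says nothing about the validity of the primary main-effect test. It should be corrected because durability is a question the article says it will examine.

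**What to change.** Exclude T1 from the short-/long-term comparison and replace the sentence with one pre-specified post-baseline contrast from the same model, with its 95% CI. The investigators must first say what short-term means:

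- if the question is persistence after the end of the intervention, use the treatment effect at T4 minus that at T3;
- if short-term means during chemotherapy, use the effect at T4 minus the average of the effects at T2 and T3.

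Report the contrast beside the visit-specific effects at T2, T3 and T4, which will show any other time pattern.

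The cost is one sentence and no new data. The downside is modest power for a partial fade: about 22% to 44% for T4 minus T3 when 10 points fall to 5. The plan should therefore add that a non-significant contrast is not evidence of sustainability and that the confidence interval carries the conclusion. For T4 minus T3 its half-width would be about 1.96 × SE, that is 8.2, 6.9 or 5.4 points at correlations of 0.3, 0.5 and 0.7.
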